### 2.6. SampleSsize

The sample size was calculated using R based on 1000 simulated versions of the study, where the power estimate is the proportion of simulated studies that gave *p* < α for the difference between the pre- and post-intervention stages. Using the Short Physical Performance Battery (SPPB) as the primary outcome measure with 50 subjects, the increased mean responses anticipated with alpha 0.01 are shown in Table 2. This is assuming the following parameters: average response at baseline 5; between-subject SD 2.5; variability in effect between subjects SD 2 (so the effect is 2.5 with SD of 2); within-subject SD of 1; and between-group SD of 2 [18].

We expect up to 60 existing residents will consent to the intervention. The site estimates that 20 new residents will enter the home during the study period, and we estimate 15 of these new residents will consent to the study. With a 20% dropout and loss to follow-up, the highest number of participants to complete the intervention is 60 participants.

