Optometry	Participants will receive an onsite, mobile assessment by an optometrist evaluating visual function (including refraction, confrontation fields, visual acuity, ocular structure (macula and optic nerve lenticular assessment, and intra-ocular pressure) to address visual impairments that may contribute to fall risk. Actions arising from the assessment of visual function may include new spectacle prescriptions or referral of participants for management of ocular disease.
Pharmacy	Participants will receive an onsite medication review by a pharmacist who will provide recommendations regarding the resident’s medication to the participant’s GP, nursing staff, and family members. After the initial medication review, participants will receive a 2-week follow-up visit to understand how medication decisions are implemented in the medication treatment and charts. Each participant will have an initial case conference and then a follow-up visit from the pharmacist every 3 months (online or in person).

**Table 2 healthcare-13-00341-t002:** Associated power based upon *n* = 50 and mean change in the SPPB.

Increase Mean Response After Intervention	Power
2.5	0.99
2	0.94
1.75	0.84
1	0.63

**Table 3 healthcare-13-00341-t003:** Outcome measure summary.

Primary Outcome Measures	
Falls: Number of falls in past 12 months Number of falls during intervention period Number of falls after intervention	
Quality of Life Aged Care Consumers (QOL-ACC) [19]	
Frailty: The Frail in Nursing Homes (Frail-NH) Scale [20] and the and Patient Health Questionnaire (PHQ9) [22]	
Short Physical Performance Battery (SPPB) [21]	
**Secondary outcome measures**	**Allied health discipline**
Short Falls Efficacy Scale—International (Short FES-I) [23]	Physiotherapy
Subjective Global Assessment (SGA) [24] Mid-arm muscle circumference [25,26] Quantitative analysis of dietary intake will be calculated before and after fortification	Nutrition and Dietetics
Canadian Occupational Performance Measure (COPM) [27]	Occupational Therapy
Number of medications (that contributed to increased risk of falls) ceased/changed at case conferences Number of case conferences and pharmacist follow-ups Rate of GP agreement on pharmacist recommendations	Pharmacy
Number of new or updated spectacles recommended Number of referrals arising from vision assessment The National Eye Institute Visual Functioning Questionnaire—25 (VFQ-25 + 10) [28]	Optometry

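### Table 2 is not a valid power curve at alpha 0.01 for the inputs in Section 2.6: its four rows imply two different standard errors

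*Protocol article*

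**What the plan says.** Section 2.6 defines power by simulation with 1000 simulated studies: "the power estimate is the proportion of simulated studies that gave *p* < α for the difference between the pre- and post-intervention stages". The SPPB is the outcome used, and "with 50 subjects, the increased mean responses anticipated with alpha 0.01 are shown in Table 2". The inputs are a baseline mean of 5, a between-subject SD of 2.5, "variability in effect between subjects SD 2 (so the effect is 2.5 with SD of 2"), and "within-subject SD of 1; and between-group SD of 2". Table 2 carries one label for every row, "Associated power based upon *n* = 50 and mean change in the SPPB", and its first column is "Increase Mean Response After Intervention". Its rows read 2.5 → 0.99, 2 → 0.94, 1.75 → 0.84 and 1 → 0.63.

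Only the mean gain is said to vary between rows. No other n, alpha or SD is given for any row. Section 3.1 names the analysis: a mixed model with stage as a fixed effect and subject as the random effect. Section 2.1 plans six groups, two baseline measurements, three during the intervention and two afterwards. Section 2.6 does not say how many visits were simulated, whether alpha is one- or two-sided, or whether the between-group SD acts on the SPPB level or on the effect.

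**The concern.** When only the mean gain changes, the precision of the estimate does not, so four powers from one correctly sized test must lie on one curve. These do not. Power falls only from 0.84 to 0.63 between 1.75 and 1 point, which is far too shallow a drop given the upper three rows.

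Table 2 is the article's only power statement. Power at the smallest listed gain governs how a null or modest SPPB result will be read, and the rows for 2 and 1.75 points show how much margin the study has if the gain falls short of the anticipated 2.5. If the figures came from a test that rejects far more often than 1% when nothing changes, they are not powers at the stated alpha.

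**Working it through.** **1. Standard error implied by each row.** With power = Φ(d/SE − z), SE = d/(z + z_power). For two-sided alpha 0.01, z = 2.576; for one-sided, z = 2.326.

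| Gain d | Stated power | z_power | SE, two-sided | SE, one-sided |
|---|---|---|---|---|
| 2.5 | 0.99 | 2.326 | 0.510 | 0.537 |
| 2 | 0.94 | 1.555 | 0.484 | 0.515 |
| 1.75 | 0.84 | 0.994 | 0.490 | 0.527 |
| 1 | 0.63 | 0.332 | 0.344 | 0.376 |

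The first three agree with one another; the fourth does not, whichever sidedness is used.

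**2. Simulation error.** With 1000 runs the 95% margin is 1.96 × √(p(1−p)/1000), at most 0.030 (at p = 0.63). Moving the powers by ±0.03 leaves the two-sided SE of the 1-point row at 0.335–0.353, against 0.449–0.511 for the 2-point row and 0.473–0.507 for the 1.75-point row. The ranges do not overlap.

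**3. The stated inputs.** Take one value before and one after. Baseline mean, between-subject SD and a group SD on the level all cancel in the change, so SE = √((2² + 1² + 1²)/n) = √(6/n). At n = 50 this is 0.346.

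| Gain | Table 2 | n = 50, normal | n = 50, t on 49 df |
|---|---|---|---|
| 2.5 | 0.99 | 1.000 | 1.000 |
| 2 | 0.94 | 0.999 | 0.999 |
| 1.75 | 0.84 | 0.993 | 0.989 |
| 1 | 0.63 | 0.622 | 0.584 |

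The 1-point row reproduces, the 2.5-point row is within a point, and 0.94 and 0.84 do not reproduce. With n = 25 (SE 0.490) the normal formula gives 0.994, 0.934, 0.840 and 0.296, close to the first three rows but not the fourth.

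**4. Between-group SD on the effect, analysed correctly.** With six groups, SE = √(6/50 + 2²/6) = 0.887. Power at 2.5 points is Φ(2.5/0.887 − 2.576) = 0.60, so the table does not come from that.

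**5. Between-group SD on the effect, subject-only random effect as in Section 3.1.** This is the nearest single set-up found. Take n = 50, one visit before and three after (an assumption).
- True SE: √((4 + 1 + 1/3)/50 + 4/6) = 0.879.
- The random-intercept model pools effect variation into the residual. The observed variance of individual changes is about 4 + 3.40 + 1.33 = 8.73, where 3.40 = 4 × (5/6) × (50/49). The visit-balance factor is 1×3/(1+3) = 0.75.
- Residual variance: (100 × 1 + 0.75 × 49 × 8.73)/149 ≈ 2.82. Model SE: √(2.82/(50 × 0.75)) = 0.274.
- The test rejects when the mean change exceeds 2.576 × 0.274 = 0.706 in size. Rejection at no effect: 2Φ(−0.706/0.879) ≈ 0.42.
- Rejection at 2.5, 2, 1.75 and 1: about 0.98, 0.93, 0.89 and 0.66.

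Simulation agrees (about 0.98, 0.93, 0.89, 0.65; null rejection up to 0.43). One visit before and two after gives about 0.97, 0.90, 0.85 and 0.60, with null rejection 0.35. The planned two baseline visits with three or five later ones fit worse, at 0.71 to 0.76 for 1 point.

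**6. Is any smooth curve close enough?** A single SE at two-sided alpha 0.01 fits Table 2 with deviance 382 on 3 df. Freeing both the slope and the critical value gives 0.98, 0.93, 0.88 and 0.61, with deviance 22.7 on 2 df (p about 0.00001) and an implied null rejection of 36%.

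**The case against.** The strongest reply is that step 1 assumes a correctly specified test, whereas Section 3.1 has subject as the only random effect although Section 2.6 simulates effects that vary between subjects. Such a model understates its standard error, inflates rejection at small effects and flattens the curve. If the group SD of 2 also sits on the effect, step 5 brings all four rows within about 4 points at one n with the listed SDs. This stands, and it rules out a stronger inference that a reader might draw: that the four rows cannot come from any one design. It does not rescue the table. The match is outside simulation error, the visit counts have to be chosen to get it, and the test behind it rejects 35 to 43% of the time under no effect, so its figures are not power at alpha 0.01.

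A reader might also infer that the true power at 1 point is about 0.30 and that 0.63 overstates it twofold. That follows only for a correctly sized paired test with the SE of the first three rows. At the stated n = 50 and SDs with one visit on each side, 0.63 is the entry that nearly reproduces. Nor does the match at n = 25 show that three rows were run with half the sample: both places that state n say 50, and the match needs one visit on each side and a normal reference.

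Finally, the design anticipates a gain of 2.5, where most readings give power of at least 0.93, and recruitment is limited by the site. The 1-point row does not set the sample size. That is fair, although the correct group-level analysis in step 4 gives only 0.60 at 2.5.

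**Conclusion.** The concern holds in this form: Table 2 is not a valid power curve at alpha 0.01 for n = 50 and the SDs in Section 2.6. The implied standard errors are 0.48–0.51 for three rows and 0.344 for the fourth (one-sided 0.52–0.54 against 0.38). The simplest reading of the inputs gives about 1.00, 1.00, 0.99 and 0.58–0.62, so two printed powers are too low on that reading. The nearest alternative gives up the stated alpha. The article does not show whether a power, an effect, n or the analysis model was mis-stated, and no row should be singled out as the wrong one.

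The calculation rests on approximate normality and a standard error that does not change with the mean gain. The sidedness of alpha, the number of visits and the place of the group SD are assumptions because Section 2.6 does not give them; none of the alternatives tried reproduced all four rows.

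**What to change.** Rerun the simulation once for all four gains with one n, the stated SDs and the planned visits before and after. Use an analysis model that carries the variation being simulated: a random stage effect by subject, and also by group if the group SD acts on the effect. Include a run at zero gain and confirm that the rejection rate is 0.01. Replace all four rows, and state n, the visits used, the sidedness of alpha and where the group SD enters. Do not write 0.30 into the 1-point row, or otherwise patch single rows, without that rerun.

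The cost is a short simulation. Some stated powers may become less favourable, most clearly if the between-group SD is meant to act on the effect.

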## Abstract

Background: Complications due to frailty and injury after falls are a significant problem for people living in residential aged care. This can lead to a range of negative outcomes including poor physical, social, and psychological well-being. The Australian Royal Commission into Aged Care Quality and Safety highlighted many aspects of care in residential aged care homes requiring improvement, leading to specific recommendations aimed at improving the outcomes in this area. This contributed to four recommendations calling for increased allied health interventions to meet the unmet needs in residential aged care. This intervention aims to implement and evaluate evidence-based allied health interventions for people living in residential aged care specifically relating to frailty, preventing falls, and maintaining engagement in everyday activities. Method: This is a pragmatic, non-randomised, pre–post design study where six groups of up to 10 residents of an aged care home will start the intervention at staggered times. The EAHOP intervention is an integrated application of a suite of allied health services (occupational therapy, physiotherapy, dietetics, speech pathology, pharmacy, and optometry), with general practitioner involvement, using allied health assistants in an integrated transdisciplinary model of care. The baseline period is 6 weeks, and intervention is a maximum of 36 weeks with follow-up at 12 and 24 weeks. Primary outcomes measure changes in falls, frailty, and quality of life. A qualitative program evaluation will be completed as well as an economic analysis. Conclusion: The results of the study will provide information about the clinical, implementation, and effectiveness outcomes of this integrated, transdisciplinary allied health service model for people living in residential aged care. The results will be used to develop evidence-informed guidelines for residential aged care providers on the delivery of allied health services.

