## 2. Methods

### 2.1. Study Design

This is a pragmatic, non-randomised, pre–post design study where six groups of up to 10 participants will start the intervention at different times. Each group will commence a baseline period lasting six weeks. Primary outcome measures will be administered in week 0 (−t_1_) of the baseline period and in week 6 (−t_2_) of the baseline period. The allied health professionals will conduct assessments using the secondary outcome measures during the baseline period, making recommendations for consideration at the case conference held with the resident’s usual General Practitioner. The prescribed allied health intervention/s will last a maximum of 36 weeks with primary outcome measures taken during the intervention period at 12 (t_1_), 24 (t_2_), and 36 (t_3_) weeks, then at 12 (t_4_) and 24 (t_5_) weeks post-intervention. The case conferences will take place in week 1 or week 2 of the intervention period. The timing of the secondary outcome measures will vary depending on the mix of interventions chosen by the allied health professional and the participant needs. See the Supplementary file for further details.

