### 2.2. Study Setting

The intervention will be conducted in a residential aged care home in Canberra, Australia, with a maximum of 60 residents.

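### The stated maximum of 60 completers needs 75 starters, but six groups of up to 10 allow only 60 starters, which leaves 48 completers at the planned 20% loss

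*Protocol article*

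**What the plan says.** Section 2.6 (Sample Size) builds up recruitment in three steps. For current residents: "We expect up to 60 existing residents will consent to the intervention". For new residents, it takes 20 arrivals over the study and adds: "we estimate 15 of these new residents will consent to the study". It then applies attrition: "With a 20% dropout and loss to follow-up, the highest number of participants to complete the intervention is 60 participants".

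The design is stated twice and in the same terms. Section 2.1 has "six groups of up to 10 participants will start the intervention at different times", and the abstract has "six groups of up to 10 residents of an aged care home will start the intervention at staggered times". Section 2.2 describes the setting as one "with a maximum of 60 residents".

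Power is given in section 2.6 and Table 2 for 50 subjects at alpha 0.01, from 1000 simulated studies with the SPPB as outcome. The four rows give power of 0.99, 0.94, 0.84 and 0.63 for mean increases of 2.5, 2, 1.75 and 1. The article does not say whether the 50 are people enrolled or people who complete.

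**The concern.** The recruitment paragraph and the group structure imply different numbers of starters. The paragraph works from 75 consenting residents, while the group structure has room for 60. Both statements are printed in the article, so this is a conflict between two figures and not a detail left to a fuller document.

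The conflict affects how the sample size is read. Someone who sets 60 completers beside the 50 used for power will conclude that there are 10 to spare after attrition. Under the stated groups and the stated 20% loss that reserve does not exist.

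**Working it through.** **Inputs (all from the protocol article)**

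- Existing residents expected to consent: up to 60 (section 2.6)
- New residents expected to consent: 15 (section 2.6)
- Dropout and loss to follow-up: 20% (section 2.6)
- Stated maximum completing: 60 (section 2.6)
- Groups: six of up to 10 (abstract, section 2.1)
- Subjects in the power calculation: 50; alpha 0.01 (section 2.6, Table 2)

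**Step 1. Reproduce the stated figure.** Completers = starters × (1 − loss).

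(60 + 15) × (1 − 0.20) = 75 × 0.80 = 60. This is an exact match. In reverse, 60 / 0.80 = 75 starters.

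**Step 2. Apply the same loss to the design.**

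Maximum starters = 6 × 10 = 60.
Maximum completers = 60 × 0.80 = 48.
Difference from the stated figure = 60 − 48 = 12, and 60 / 48 = 1.25, an overstatement of 25%.

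**Step 3. Compare with the 50 used for power, if these are completers.**

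- Margin implied by section 2.6: 60 − 50 = 10.
- Margin under the group structure: 48 − 50 = −2.
- Starters needed for 50 completers at 20% loss: 50 / 0.80 = 62.5, so 63.
- Largest loss that still leaves 50 of 60: 1 − 50/60 = 16.7%.

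**Step 4. Effect on power of 48 instead of 50.** The simulation model is not given, and simple calculations from the stated SDs do not reproduce all four rows of Table 2. I therefore took the standard error (SE) that each row implies and rescaled it, assuming a two-sided alpha of 0.01 and a normal approximation:

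SE at 50 = change / (2.576 + z of the stated power)
SE at 48 = SE at 50 × √(50/48) = SE at 50 × 1.0206
Power at 48 = Φ(change / SE at 48 − 2.576)

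| Mean increase | Stated power, n = 50 | Implied SE, n = 50 | Power at n = 48 |
|---|---|---|---|
| 2 | 0.94 | 0.484 | 0.929 |
| 1.75 | 0.84 | 0.490 | 0.822 |

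For the 1.75 row: 1.75 / (2.576 + 0.994) = 0.490; 0.490 × 1.0206 = 0.500; Φ(1.75/0.500 − 2.576) = 0.822.

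The losses are 1.1 and 1.8 percentage points. With 1000 simulations, the 95% Monte Carlo margin is 1.96 × √(0.94 × 0.06/1000) = 1.5 points at 0.94 and 1.96 × √(0.84 × 0.16/1000) = 2.3 points at 0.84. Both losses lie within the simulation error of the printed values.

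**The case against.** **The 50 need not be completers.** This is the strongest reply, and it stands. Section 2.6 speaks only of subjects. Section 2.7 keeps data from non-completers up to withdrawal, section 2.1 measures at weeks 12, 24 and 36 of the intervention, and section 3.1 plans a mixed-effects model with imputation as a sensitivity analysis. Someone who leaves after week 12 can contribute both pre- and post-intervention data, so 60 starters could supply 50 analysable subjects. A reader might infer from the 48 that the sample size behind Table 2 is out of reach. The article does not support that without qualification.

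**The figures are ceilings.** This is true, but the ceiling itself is what fails: with every place filled, 20% loss leaves 48.

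**New residents could refill vacated places, or the 20% could be lost between consent and start.** Refilling might reconcile 75 with groups of 10, but the article nowhere provides for it. The second reading takes 75 consents to 60 starters, but then nobody is lost during up to 36 weeks of intervention, whereas the sentence counts people who complete it.

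**The setting and turnover.** A reader might go further and argue that 60 existing residents means 100% consent, or that 20 arrivals in a full home mean 20 departures (20/60 = 33%) and only about 40 completers. Neither is supported. The limit of 60 in section 2.2 may describe the home or the study, and the expected consent is worded as an upper bound. The turnover argument further assumes that the home is full, that those who leave are participants, and that departures over the whole staggered study equal losses during one person's intervention.

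**Conclusion.** The maximum of 60 completers in section 2.6 is not compatible with the design in the abstract and section 2.1. At the plan's own 20% loss, six groups of up to 10 yield at most 48, so the printed figure is 12 too high. This rests only on the article's numbers and on the absence of any provision for refilling places, larger groups or a further group.

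The consequence for power is conditional and small. If the 50 in Table 2 are completers, an apparent reserve of 10 becomes a shortfall of 2, at a cost of about one to two percentage points of power in the rows checked. If they are enrolled participants, or people with any post-baseline data, 60 starters can cover them. The point is therefore a misstated sample-size figure and a margin that the design does not provide; it is not a finding that the study is underpowered.

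**What to change.** Reconcile section 2.6 with the abstract and section 2.1. The article does not show which statement governs, so the authors should choose:

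1. If the group structure holds, state at most 60 starters and 48 expected completers at 20% loss, and remove 60 as the number completing.
2. If 75 are meant to start, correct the number or size of the groups (75/10 = 7.5, so eight groups of 10; or 75/6 = 12.5, so six groups of up to 13), or state that vacated places will be refilled and how.

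In either case, state whether the 50 in Table 2 are enrolled or completing. If they are completing and option 1 applies, rerun Table 2 at 48.

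Option 1 costs a change of wording and, at most, a rerun of an existing simulation. It needs no extra participants, and the stated completers and power become slightly less favourable. Option 2 changes the stated design and would need the capacity to deliver the intervention to the additional starters.

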### 2.7. Data Collection and Monitoring

Data collection forms will be available on the RedCap data management system where the relevant allied health professional or Clinical Liaison Manager will enter the data as each outcome measure is completed. Data from participants who do not complete the intervention will be collected up until the time they withdraw from the study. An independent Project Governance Committee will be established to meet quarterly with a function to monitor the data collection procedures and to monitor reported adverse events. Adverse events will be reported by any member of the research team or the aged care provider on an adverse events form that will be stored electronically on a secure server and available in hard copy from the aged care provider.

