### 2.3. Participants

Any new or existing (permanent) resident of the residential aged care home is eligible. Staff at the home will approach any new or existing resident and/or family with a study flyer. The research team will present the study to the residents at the regular residents’ meeting. Participants will register their interest through a register kept by the nursing staff at the home and/or they will be able to contact the research team through contact details listed on the flyer and promotional material posted at the home. All participants and/or their carers, power of attorney, or guardian will be required to give written consent after reading the relevant participant information at which time the Clinical Liaison Manager (who is a Registered Nurse) will consent them into the study and assign them a study number. Residents with a diagnosis of dementia or identified by care staff as experiencing cognitive impairment are eligible. All participants will be screened for cognitive function using the Psychogeriatric Assessment Scale (PAS) [13]. There is no cutoff score for inclusion; however, in some cases, people with severe cognitive impairment will not be able to engage in the allied health program. For example, people who have severe expressive and receptive communication impairment and who are immobile due to dementia. For those residents with severe dementia or on an end-of-life pathway, we will liaise with the relevant medical team and/or staff Registered Nurse to determine if these residents should ethically be considered for the program. Residents who elect not to participate in the intervention will receive their usual medical, health, and lifestyle services as usual.

Participants will be able to discontinue the intervention at any time at their, or their Enduring Power of Attorney’s, request. Participants will be withdrawn from the study if any deterioration in their medical condition makes participation unsafe in the opinion of their General Practitioner.

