## 3. Data Analysis

### 3.1. Quantitative Analysis

All statistical analysis will be conducted using R version 4.2.1 (23 June 2022) in Rstudio (version 2023.6.2.561). Baseline demographic and descriptive statistics will be summarised for each group prior to the intervention starting (control phase). Primary outcome measures will be collected twice in the control period at week 0 and week 6. Primary outcome measures will be collected every 12 weeks during the intervention (weeks 12, 24, and 36) and at 12 weeks and 24 weeks post-intervention for each group. Categorical data will be summarised using frequency statistics and will be visualised. Continuous and other numerical data will be visually explored and summarised using sample descriptive statistics, selected as appropriate based on apparent distributions. A mixed-effects model will be computed, with treatment stage (i.e., pre- vs. post-intervention) as a fixed effect and subject as a random effect. Sensitivity analyses will be conducted, which will impute missing data using the “mice” package (version 3.15.0) [34].

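### Residents withdrawn for deterioration have no data after withdrawal, which tilts the uncontrolled pre-post contrast towards benefit; imputation with mice in its usual form would correct this partly or not at all

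*Protocol article*

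**What the plan says.** Section 2.3 of the protocol article gives two exits. One is by request and concerns the intervention: "Participants will be able to discontinue the intervention at any time at their, or their Enduring Power of Attorney’s, request". The other is clinical and concerns the study: "Participants will be withdrawn from the study if any deterioration in their medical condition makes participation unsafe in the opinion of their General Practitioner".

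Section 2.7 sets the data rule: "Data from participants who do not complete the intervention will be collected up until the time they withdraw from the study".

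Section 2.6 plans for loss: "With a 20% dropout and loss to follow-up, the highest number of participants to complete the intervention is 60 participants". It gives no breakdown by reason.

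Section 3.1 specifies a mixed model "with treatment stage (i.e., pre- vs. post-intervention) as a fixed effect and subject as a random effect". On missing data it says "Sensitivity analyses will be conducted, which will impute missing data using the" mice package, and names no assumption about the missingness.

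Section 2.8 states that the home records every fall and that the research team will have access to those records.

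**The concern.** Read together, sections 2.3 and 2.7 make a poor health course the trigger for losing later outcomes. The outcomes lost are those that deterioration worsens: SPPB, Frail-NH, QOL-ACC and falls. The effect is a pre versus post contrast in one home. No parallel group is measured on these outcomes, so nothing would show the same loss occurring without the intervention. If the residents who decline leave the post stage, the remaining post data look better than the enrolled group really is, and the difference is read as an intervention effect.

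For falls the loss is avoidable, because the source is a routine record that exists whether or not the resident is still in the study. SPPB, Frail-NH and QOL-ACC values that are never collected cannot be recovered later.

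**Working it through.** **The plan's own figure.** Section 2.6 expects up to 60 existing and 15 new residents to consent. (60 + 15) × (1 − 0.20) = 60 completers, which reproduces the stated number. The planned loss is 75 × 0.20 = 15 residents.

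**Bias if decline occurs at withdrawal.** Assumptions, none of them given in the documents:
- no treatment effect;
- a share p of enrolled residents drops by D SPPB points at withdrawal and is unmeasured afterwards;
- withdrawal times are uniform over the 36 weeks.

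The target is the mean change in all enrolled residents. By weeks 12, 24 and 36, fractions 1/3, 2/3 and 1 of the withdrawals have happened; at the two post-intervention visits the fraction is 1. The data kept show a change of about 0, so the bias equals the decline left out:
- week 36: p × D;
- weeks 12, 24 and 36 pooled: p × D × (1/3 + 2/3 + 1)/3 = 0.667pD;
- all five later visits pooled: p × D × (1/3 + 2/3 + 1 + 1 + 1)/5 = 0.8pD.

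With p = 0.20 these are 0.20D, 0.13D and 0.16D. With p = 0.10 (half of the 20%) they halve.

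| D | Week 36 (p = 0.20 / 0.10) | Weeks 12–36 pooled | Five visits pooled |
|---|---|---|---|
| 1 | 0.20 / 0.10 | 0.13 / 0.07 | 0.16 / 0.08 |
| 2 | 0.40 / 0.20 | 0.27 / 0.13 | 0.32 / 0.16 |
| 3 | 0.60 / 0.30 | 0.40 / 0.20 | 0.48 / 0.24 |

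A simulation with 60 residents and p = 0.20 gave week-36 estimates, truncated versus continued, of 0.00 versus −0.19 (D = 1), 0.01 versus −0.40 (D = 2) and −0.01 versus −0.60 (D = 3), in line with 0.2D.

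**Does imputation expose it?** A second simulation used section 2.6's inputs (baseline mean 5, between-subject SD 2.5, effect SD 2, within-subject SD 1), with 75 enrolled, 15 lost, two pre and five post visits, and a true effect of 0. Each setting had 150 replicates, so the second decimal is approximate. The imputation was sequential regression on earlier visits, which is missing-at-random (MAR).

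| Who is lost | Mixed model | MAR imputation |
|---|---|---|
| Random residents | 0.01 | 0.00 |
| Half the losses are the worst responders, all lost before week 12 | 0.37 | 0.36 |
| All are the worst responders, lost before week 12 | 0.71 | 0.72 |
| All are the worst responders, lost at staggered visits | 0.25 | 0.15 |

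The 0.71 agrees with the truncated-normal mean shift 2 × φ(z)/(1 − 0.20) = 0.70, where z is the 20th percentile of the standard normal. When loss comes before any post-stage measurement, imputation repeats the biased answer. When some post-stage data come first, it recovers part.

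**Fall counts.** With uniform withdrawal, a withdrawn resident loses on average half of the 36 weeks: 0.20 × 0.5 = 0.10 of total exposure if all dropout is GP-initiated withdrawal, less otherwise.

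**The case against.** **Stopping the intervention versus leaving the study.** A reader might infer that the protocol treats these as one event, so that everyone who stops is lost. Section 2.3 does not support that. It separates discontinuing the intervention from withdrawal from the study, and section 2.7 ends collection only at the latter. Read literally, someone who stops on request but has not left the study stays in data collection. The concern is confined to GP-initiated withdrawal.

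**The imputation.** A reader might infer that the sensitivity analysis cannot reveal the bias. The article names a package and no assumption. MAR is an inference from its usual use; mice can also run delta-adjusted imputation, and an analysis plan not shown may specify it. Even under MAR, the staggered case moved from 0.25 to 0.15. What stands is that usual-form imputation corrects only partly or not at all, and that no later analysis plan restores data which section 2.7 stops collecting.

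**The size.** Setting 0.2 to 0.6 points against 1 point, the lowest row of Table 2, would overstate the case. That range is a week-36 figure and takes all dropout as deterioration, whereas section 2.6 gives no reasons and section 2.3 allows stopping on request. Section 3.1 fits a single pre/post stage effect, so the pooled figures may be nearer. Section 2.6 also states an assumed effect of 2.5, of which 0.6 is 24%.

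**Hospital leave days.** These are not uncontrolled: section 2.10 compares them with a matched sample. One-sided truncation could still distort that comparison, but by a different route, and the article does not say whether the comparison sample is truncated.

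**Design.** Selective loss is a familiar limitation of a pragmatic single-home pre-post study. That tempers how serious the point is, but here the loss follows from two written rules and is avoidable for falls.

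**Conclusion.** The concern holds for residents withdrawn because the GP judges participation unsafe. Their data end at that point by the stated rules, and the direction of the bias favours the intervention on falls, frailty, SPPB and quality of life. The size is an assumption range, not a finding from the documents. With no treatment effect, D = 1 to 3 and uniform timing, it runs from about 0.07 SPPB points (D = 1, half of dropout is deterioration, weeks 12–36 pooled) to 0.60 (D = 3, all of dropout, week 36). Bias is nil if the losses are unrelated to outcome. For falls, up to about 10% of exposure over 36 weeks is lost from raw counts. Using person-time corrects the exposure but not the selective loss of time from residents who may be falling more.

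**What to change.** - **Section 2.3:** leave the clinical rule as it stands. This point does not require outcome visits after GP-initiated withdrawal, since that would touch the rule's scope.
- **Section 2.7:** state that after GP-initiated withdrawal, unless consent for data use is withdrawn, falls continue to be extracted from the home's routine records to t5, the last scheduled follow-up. Do the same for hospital leave days and death where the home records them. Record the reason for each withdrawal, so that the share due to deterioration is known.
- **Falls analysis:** use rates over observed person-time, not raw counts.
- **Section 3.1:** add a delta-adjusted imputation in mice for SPPB, Frail-NH and QOL-ACC in residents withdrawn for deterioration (for SPPB, for example, 1, 2 and 3 points worse after withdrawal), and report the tipping point at which the conclusion changes.

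The cost is consent and ethics wording, routine record extraction, and some analysis code.
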